# Evaluation of a novel technology-supported fall prevention intervention – study protocol of a multi-centre randomised controlled trial in older adults at increased risk of falls

**DOI:** 10.1186/s12877-023-03810-8

**Published:** 2023-02-18

**Keywords:** Fall prevention, Technology-based, Randomised controlled trial, RCT, Robot device

## Abstract

**Background:**

Increasing number of falls and fall-related injuries in an aging society give rise to the need for effective fall prevention and rehabilitation strategies. Besides traditional exercise approaches, new technologies show promising options for fall prevention in older adults. As a new technology-based approach, the hunova robot can support fall prevention in older adults.

The objective of this study is to implement and evaluate a novel technology-supported fall prevention intervention using the hunova robot compared to an inactive control group. The presented protocol aims at introducing a two-armed, multi-centre (four sites) randomised controlled trial, evaluating the effects of this new approach on the number of falls and number of fallers as primary outcomes.

**Methods:**

The full clinical trial incorporates community-dwelling older adults at risk of falls with a minimum age of 65 years. Including a one-year follow-up measurement, all participants are tested four times. The training programme for the intervention group comprises 24-32 weeks in which training sessions are scheduled mostly twice a week; the first 24 training sessions use the hunova robot, these are followed by a home-based programme of 24 training sessions. Fall-related risk factors as secondary endpoints are measured using the hunova robot. For this purpose, the hunova robot measures the participants’ performance in several dimensions. The test outcomes are input for the calculation of an overall score which indicates the fall risk. The hunova-based measurements are accompanied by the timed-up-and-go test as a standard test within fall prevention studies.

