This paper describes a study protocol that aims to evaluate the effects of a complex fall prevention intervention on fall incidence and fall risk in older persons with an increased fall risk. The intervention comprises two consecutive components; a technology-supported exercise programme followed by a home-based exercise programme. Based on a randomised controlled design, the study will evaluate the hypotheses that the intervention reduces fall incidence (primary outcome) and fall risk (secondary outcome).

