**Fig. 1 Fig1:**
[figure not shown]
SPIRIT-Figure: Schedule of enrolment, interventions, and assessments (CTR = control group; HBEP = home-based exercise programme; INT = intervention group; TSEP = technology-supported exercise programme; X = relevant for INT and CTR; +  = only relevant for INT)

For the intervention group, T_0_ is a baseline assessment; T_1_ an assessment after finishing the technology-supported part of the intervention; T_2_ an assessment after finishing the home-based exercise programme; and T_3_ a final follow-up assessment 12 months after T_2_. In total, the training period of the intervention group comprises 2*24 units (48 sessions in total) with a training frequency of two planned training sessions of 30 min each per week. The intervention period of the technology-supported exercise programme is individually dependent on the time progress of the completed 24 sessions. Given the defined training frequency of two training sessions per week, the technology-supported exercise programme has a minimum intervention period of 12 weeks. If individual training sessions are cancelled, the intervention period may be extended, however, it is limited to a maximum of 16 weeks. Identical to the intervention period of the technology-supported exercise programme, the period of the home-based programme is then determined individually for each participant. Participants in the control group receive all four measurements. Participants in the control group are not offered any actions; they are instructed to maintain their activities as usual. The time periods between the T_0_, T_1_ and T_2_ measurements are defined as 16 weeks for the control group. Both groups end at T_3_ with a final follow-up assessment 12 months after T_2_. Figure 2 shows the detailed timeline for study participants. Participants in the control group will have the opportunity to participate in an optimized training programme using the hunova robot after the end of the study.

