#### Silver Index (SI)

Inputs into the SI are age, number of falls in the last 12 months, and the outcomes of following 8 tests for gait, balance, and rising from a chair (for detailed test procedures, and the calculation of the SI, see [35]:

Gait:
1. a 6-m walk test is used for determining gait speed;

Balance control is tested while the participant is standing on a force platform (foot platform) under the following conditions:2. quiet standing with eyes open on static foot platform (30 s);3. quiet standing with eyes closed on static foot platform (30 s);4. standing with eyes open on an unstable foot platform (responding to the participant’s postural oscillations; 30 s);5. standing with eyes open while the foot platform is moving along a default trajectory (30 s);6. reactive balance: standing with eyes open while the foot platform implements specific perturbations (with impulses of 6 degrees in random directions and in random order;7. limits of stability test: the person is instructed to move his/her body’s centre of mass as far as possible in anterior–posterior and medio-lateral directions without needing to step to maintain balance;

Muscle function (lower extremities):8. the Five Times Sit to Stand Test (FTSST) is used as a functional test for lower extremity muscle function.

Based on these tests, the SI indicating fall risk was calculated [35]. SI ranges between 0 and 100%, a score higher than 40% is considered to indicate an increased fall risk and is used as inclusion criteria for participation in this study. In addition to the overall SI, the hunova robot compares the results of seven dimensions (static balance, dynamic balance, reactive balance, limits of stability, gait speed, sensory integration, and sit to stand) to a reference sample of the same age. Based on this comparison, each dimension is defined as normal (on average) meaning no deficit or having a performance below average resulting in a yellow (poor performance), orange (very poor performance), or red deficit (very very poor performance) for this dimension. The dimensions (and deficits) are visualised in a radar plot (see Fig. 3). These dimensions and deficits are relevant for the planning of the training sessions within the intervention (see ‘intervention’).

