### Intervention

#### Technology-supported exercise programme (TSEP)

The first intervention period refers to the technology-supported exercise programme (TSEP) using the hunova robot (Movendo Technology, Genoa, Italy). The hunova robot is a programmable robotic medical device that consists of two electromechanical platforms with two degrees of freedom, one at foot level (foot platform) and one at seat level (seat). Both platforms include two motorized axes. The platforms are rigidly connected to the robot movement axes by means of a torque and force sensor (6-axis sensor). The system allows two degrees of freedom of mobility (forwards-backwards = anterior-posterior and left-right = medio-lateral). The hunova robot can operate in static, active, passive, and assistive modes. Further details can be found in additional file 1. The hunova robot operates in conjunction with a wireless sensor (Inertial Movement Unit - IMU) located on the participant’s torso, to monitor torso motion. All exercises are accompanied by graphical and audio applications (providing biofeedback) run by the remote computer, with which the participant interacts to complete the exercises.

The participants are supervised in a 1:1 situation by a sport or physio-therapist for about 30 min per training session. By performing various functional, balance, and strength exercises on the hunova robot, the participants train within their individual deficit areas of balance and muscle strength while receiving visual feedback via a monitor.

The design of the TSEP training is planned and carried out on three levels. The first level is represented by the training areas, the second level is the type of activity and the third is the difficulty of each activity. The TSEP is the result of the combination of the three layers and the detailed description is provided in the following paragraphs. At first, there is the training layer (level 1), based on the seven subsections of the SI supplemented by a maintenance area, which consists of exercises that train the seven functional areas assessed. These eight training areas are named static balance, dynamic balance, sensory integration, reactive balance, gait speed, limits of stability, sit to stand and maintenance. For each dimension, specific exercises are possible with the hunova robot. A detailed description of all exercises implemented within the TSEP using the hunova robot is presented in Table 1.

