**Table 1 Tab1:** Exercise list and descriptions (COP = centre of pressure)

Training area (level 1)	Task description	Position	Mode	Difficulty regulation (level 3)
Static balance	Participant / exercising person must maintain balance while shifting her/his COP through whole body movements	Standing bipodal or standing with one leg on foot platform, one behind	Static foot platform	- load on one leg - hands/torso reaching - inclined plane - dual task exercises - squats - leg raises
Dynamic balance	Participant / exercising person must maintain balance while the foot platform simulates changing terrain and moves in predefined directions/patterns	Standing bipodal or standing with one leg on foot platform, one behind	Active foot platform	- load on one leg - variation in movement planes - higher amplitude of motion - hands reaching - dual task exercises
Sensory integration (dynamic balance + visual integration)	Participant / exercising person must maintain balance on various simulated surfaces using visual-motor or proprioceptive integration	Standing bipodal or sitting	Static, active, passive foot platform, active, passive seat	- eyes closed - reaching - unstable surface - dual task exercises
Reactive balance	Participant / exercising person must maintain balance while the foot platform is movable and follows her/his movements	Standing bipodal or standing with one leg on foot platform, one behind	Active, passive foot platform	- load on one leg - hands/torso reaching - dual task exercises - platform gives impulses
Gait speed (dynamic balance + reactive balance)	Participant / exercising person must maintain balance while the foot platform simulates changing terrain or follows her/his movements	Standing bipodal or standing with one leg on foot platform, one behind	Active, passive foot platform	- load on one leg - platform gives impulses - torso/hands reaching - variation in movement planes
Limits of stability	Participant / exercising person must maintain balance while moving her/his COP through whole body movements following predefined patterns	Standing bipodal	Static, active, passive foot platform	- reaching (with load) - higher amplitude of motion - variation in movement planes - variation in movement patterns

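### The Silver Index is measured largely on the robot that only the intervention arm trains on, so an isolated Silver Index gain, above all at T1, does not by itself show reduced fall risk

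*Protocol article*

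**What the plan says.** The Background sets out two hypotheses: "the study will evaluate the hypotheses that the intervention reduces fall incidence (primary outcome) and fall risk (secondary outcome". The Abstract and the section Silver Index (SI) make the SI the overall score that indicates fall risk. The section Planned statistical evaluation of outcomes lists SI and TUG as the secondary outcomes, both analysed by a 2 × 4 (group by time) ANOVA/ANCOVA.

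The outcome and the treatment share a device. On the outcome, the Abstract says: "Fall-related risk factors as secondary endpoints are measured using the hunova robot". On the treatment, it says: "the first 24 training sessions use the hunova robot". The section on the technology-supported exercise programme (TSEP) describes its training layer as "based on the seven subsections of the SI supplemented by a maintenance area, which consists of exercises that train the seven functional areas assessed".

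The control arm has no such exposure. Under Study design: "Participants in the control group are not offered any actions; they are instructed to maintain their activities as usual". Controls meet the robot only when tested: "Participants in the control group receive all four measurements".

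The Abstract and Expected key results anticipate the first favourable changes in risk factors once the 24 robot sessions are complete, that is, at T1.

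**The concern.** When one arm practises for weeks on the apparatus that later scores the outcome, part of any gain may be skill with that apparatus: knowing how the platform moves, reading its feedback, being at ease on it. Randomisation does not remove this, because the practice is itself the difference between the arms. If the SI improves and nothing off the device does, the plan as written would still let the result count in favour of the fall-risk hypothesis. Any such bias runs towards the intervention. What is at stake is the meaning of a secondary result, not the primary comparison of falls and fallers.

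**Working it through.** The plan states no figure on this point, so there is none to reproduce. The check sets the tests beside the training.

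**1. How much of the SI is done on the platform.** The section Silver Index (SI) lists age, falls in the last 12 months and eight tests. Tests 2-7 are done standing on the platform, which is 6 of 8 tests. Test 1 (6-m walk) and test 8 (Five Times Sit to Stand Test) are not described as platform tasks.

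**2. Test against training task (Table 1).**

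| SI test | Nearest TSEP task |
|---|---|
| 2: quiet stance, fixed platform | Static balance: fixed platform, but with deliberate weight shifts |
| 3: eyes closed | Sensory integration: eye closure is one way to raise difficulty |
| 4: unstable platform responding to sway | Reactive balance: platform follows the person's movement |
| 5: "standing with eyes open while the foot platform is moving along a default trajectory (30 s" | Dynamic balance: the person "must maintain balance while the foot platform simulates changing terrain and moves in predefined directions/patterns" |
| 6: perturbation impulses | Reactive balance and gait speed: platform impulses raise difficulty |
| 7: leaning to the limits of stability | Limits of stability: shifting the centre of pressure along set patterns |

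The resemblance is close for most rows. Nowhere does the article say that test and exercise are identical.

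**3. Difference in exposure.** The TSEP section plans 15 min net per session: 24 × 15 min = 360 min = 6 h in the intervention arm, 0 h of training in controls. Both arms have the same four test occasions.

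**4. How that exposure is spread.** Each session focuses on one dimension, and over the programme the two worst dimensions are scheduled. The 6 h are not spread over all six platform tests.

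**5. What the analysis can estimate.** Let b be the transferable benefit and f the familiarity gained by training. The difference between arms in SI change is b + f, since the retest effect common to both arms cancels. The group-by-time model estimates that sum only. The named covariates (demographics, physical activity, health) do not measure device practice, and no control has any robot training.

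**6. Timing.** T1 follows directly on robot training. T2 comes after the home programme, whose length matches the robot phase (12 to 16 weeks). T3 is 12 months later. Familiarity is therefore likely to be greatest at T1.

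**7. Sensitivity illustration, on an assumed effect.** The documents give no SI standard deviation or practice effect. Suppose familiarity alone shifts the SI by d standard deviations with no true change in fall risk. Take 181 evaluable people in two equal arms and one unadjusted comparison at two-sided 5% (the article does not state sidedness). The noncentrality is d × √(181/4) = 6.73d.

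| Assumed d | Noncentrality | Chance of significance |
|---|---|---|
| 0.1 | 0.67 | about 10% |
| 0.2 | 1.35 | about 27% |
| 0.3 | 2.02 | about 52% |
| 0.4 | 2.69 | about 77% |
| 0.5 | 3.36 | about 92% |

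With 235 × 0.70 ≈ 164 evaluable, d = 0.2, 0.3 and 0.4 give about 25%, 48% and 73%. These values are power for an assumed d; they do not estimate what will happen in this trial.

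**The case against.** The case on the other side is substantial.

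- **Scope.** A reader might infer that the intervention arm rehearses the SI tests themselves and that six of eight tests are inflated. The documents do not support that. Only two dimensions per person are scheduled, and Table 1 includes one-leg, seated, reaching, dual-task and squat variants that are not SI tests. A count of tests is also not a share of the score, because the SI uses age, fall history and two off-platform tests, and its weights are not given. This stands.
- **Size.** A reader might take the percentages above as a false-positive rate. They are not: d is assumed, and the calculation is not the planned model with Bonferroni post-hoc tests. This stands too.
- **Existing safeguards.** TUG is already a secondary outcome at all four visits with the same analysis, SI is repeated at T2 and T3, and the primary outcomes are falls recorded by diary. These limit the harm. They do not say what will be concluded if SI and TUG disagree.
- **TUG is no clean yardstick.** Gait speed and sit-to-stand are training areas as well, and the assessors are the unblinded training therapists. This is true, but neither TUG nor the 6-m walk is described as a platform task, so device familiarity has a much less direct route into them.
- **Left to the analysis plan.** An interpretation rule may sit in a document not shown. However, sharing the device between treatment and outcome is a stated design choice, and the article has its own section on limitations and risk of bias. That section covers selective recruitment, unblinded assessment, physical activity and health status, but not device familiarity.

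**Conclusion.** The point holds in a bounded form. The SI is measured largely on the device that only the intervention arm trains on, in areas built on the SI dimensions and with tasks resembling tests 2-7. The planned analysis cannot tell familiarity from transferable benefit, and the limitations do not mention it. An SI gain standing alone, above all at T1, is therefore weak evidence of reduced fall risk.

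The documented size is the contrast in exposure: about 6 h of planned net device training against none. Neither the affected share of the score nor the familiarity effect can be computed from the article. That familiarity is greatest at T1 is a judgement from timing, not a documented fact.

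A reader might go further and conclude that a positive SI result would be spurious, or that the trial's main conclusion is compromised. Neither follows: a real benefit is equally compatible with an SI gain, and falls and fallers are recorded off the device.

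**What to change.** All four changes use data already collected.

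1. State in advance that an SI gain, above all at T1, without a gain in TUG or 6-m gait speed will not be concluded to be reduced fall risk.
2. Report the platform components (tests 2-7) separately, labelled as performance on the trained device, beside the off-platform ones (6-m walk, Five Times Sit to Stand Test).
3. Base any claim of a lasting SI benefit on T2 and T3.
4. Add device familiarity to the limitations.

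TUG need not be ranked above the SI. The trial is registered and recruiting, so re-ordering outcomes would be a documented mid-trial change, and the problem can be handled without it. The rule in item 1 should be dated and in place before SI results are compared by arm.

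The cost is a few sentences and one extra table. The downside is small: a positive SI result alone supports a weaker claim, and TUG may show a smaller effect and is itself measured by unblinded therapists.

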**Discussion:**

This study is expected to lead to new insights which may help establish a new approach to fall prevention training for older adults at risk of falls. First positive results on risk factors can be expected after the first 24 training sessions using the hunova robot. As primary outcomes, the number of falls and fallers within the study (including the one-year follow-up period) are the most relevant parameters that should be positively influenced by our new approach to fall prevention. After the study completion, approaches to examine the cost-effectiveness and develop an implementation plan are relevant aspects for further steps.

**Trial registration:**

German Clinical Trial Register (DRKS), ID: DRKS00025897. Prospectively registered 16 August 2021, https://drks.de/search/de/trial/DRKS00025897.

**Supplementary Information:**

The online version contains supplementary material available at 10.1186/s12877-023-03810-8.

## Background

Age-associated changes in functioning lead to a higher incidence of falls in older adults. Studies indicate that approximately one in three adults (i.e., more than 30%) aged at least 65 falls once per year [1–3]. With increasing age after 65, or in the presence of specific age-related diseases, fall risk may even increase beyond 50% [1–3]. The individual consequences of falls may comprise fall-related injuries, subsequent activity restriction, and fear of falling [4–6]. In addition to individual costs, the societal costs of falls are enormous; for Germany, direct health care costs after a fall-related fracture of the femoral neck have been estimated at approximately 15 k euros per person [7]. According to estimates, the costs of direct medical treatment of hip fractures in Germany are more than one billion euros per year, not including long-term nursing costs and indirect costs such as time lost from work by relatives [8]. Thus, it is paramount to prevent older persons from falling. Fall risk is associated with measures from multiple domains; these include not only measures of cognitive and physical functioning but also gender, age, presence of co-morbidities, medication use, fear of falling, and environmental factors [9]. Not all variables associated with the incidence of falls can be influenced (e.g., gender, age). However, some of the most important predictors of fall risk, such as muscle function, balance control, and gait quality, can be improved by appropriate fall prevention interventions [10, 11].

Reviews of available studies demonstrate that effective fall prevention strategies simultaneously address different risk factors [10, 12, 13]. Exercise-based strategies are most effective when they combine balance and functional exercises plus resistance exercises [10]. Particularly, the integration of activities that are important for daily life functioning, such as rising from a chair are essential. According to current evidence, an exercise programme needs to have a minimal duration and has to be challenging in intensity to be effective in reducing the fall incidence [10]. Among the current challenges to prevent falls in older persons are a timely identification of persons at risk, as well as ensuring older persons’ participation and adherence to appropriate fall prevention programmes. To realise optimal effects, the type of exercises and their dosing should preferably be individualised, and the person should participate over a sufficiently long duration [14–16]. However, there is a large gap between evidence about effective fall prevention interventions and their transfer into clinical practice and preventing initial falls [17, 18]. In their review, Michael et al. [19] analysed the barriers most often noted by providers of primary care-relevant interventions to prevent falls. The participants (physicians) suggested that they would be more convinced to act in regard to fall prevention for older adults if they have actual data about falls of their patients and an effective fall-risk assessment and treatment. Furthermore, they would prefer information where they can refer high-risk patients to receive effective fall prevention [19]. With our study protocol we aim to address these omissions.

Miscellaneous new technology can contribute to the assessment of fall risk [20–22] as well as the implementation of novel fall prevention interventions [23–28]. Furthermore, stepping interventions [29] and perturbation-based interventions [30] are implemented to prevent falls. The effects of robot-assisted approaches using exoskeletons and (end-effector) robots on fall-related risk-factors have already been studied in different disease groups (multiple sclerosis, stroke, Parkinson’s disease) (e.g., [31–33]). However, there still is little information about the use of robotic devices to prevent falls in older adults. Only one study by Verrusio et al. [34] used robotic technology for fall prevention training with healthy older adults. Their results showed first positive effects of using the exoskeleton human body posturizer regarding fall incidence in older adults without any diseases [34].

The present study protocol aims to evaluate the contribution of such new technology to the prevention of falls. Recent developments have led to technology that can be used to assess individual fall risk profiles and/or implement exercise programmes which aim to address individual risk profiles [22, 26]. One specific example of such systems is the hunova robot (Movendo Technology, Genoa, Italy), a robotic medical device for the evaluation of sensory-motor functions and rehabilitation after injuries of ankle, lower leg, or trunk. By measuring various aspects of balance and lower limb functioning, the hunova device creates an individual fall risk profile and identifies deficient dimensions on which an individualisation of the training programme takes place. During the training sessions, participants receive live feedback on a screen, which can be implemented directly. All details can be found in Cella and colleagues and Saglia et al. [35, 36]. First clinical studies have demonstrated positive results in the rehabilitation of stroke patients, as well as in patients with Parkinson’s disease (PD) [37, 38]. As a new approach, we use a novel technology (hunova robot), developed and used previously for specific diseases, now moving into older adult research, particularly fall prevention.

This paper describes a study protocol that aims to evaluate the effects of a complex fall prevention intervention on fall incidence and fall risk in older persons with an increased fall risk. The intervention comprises two consecutive components; a technology-supported exercise programme followed by a home-based exercise programme. Based on a randomised controlled design, the study will evaluate the hypotheses that the intervention reduces fall incidence (primary outcome) and fall risk (secondary outcome).

